## Informed consent

Before enrolling patients in the trial, the investigating doctor will completely and comprehensively describe the purpose, procedure, and potential risks of this trial in writing to the patient themselves or their designated representative. Patients will be informed that they have the right to withdraw from the trial at any time. Each patient must provide written informed consent before participating in this study; this consent will be kept in the study file.

## Quality control

Quality assessment will be conducted in the following aspects in this trial: the progress of the trial; the qualifications of the investigators; the mastery of the program; the authenticity, accuracy, and completeness of the CRF; archival preservation; program implementation; AEs; drug preservation and storage; written informed consent; participant compliance; and laboratory examination data. In particular, the authenticity and accuracy of the CRF, program implementation, and determination of AEs will be strictly inspected.

### Data management

The patients in this trial will be recruited patients. Therefore, the original data will include the CRF, patient log card, original laboratory examination, and written informed consent. The inspector will regularly visit all centers to conduct a data quality inspection. The authenticity and accuracy of data will be checked by original laboratory comparison, telephone follow-up with patients, and examination of the integrity, timeliness, and normalization of data. The paper form of the data will be collected after approval inspection. The researcher who is responsible for data entry will build an EpiData-based database with double-recorded data entry by two people and consistency testing will be carried out to ensure the accuracy of data.

### Data analysis

Data analysis will be performed by professional statisticians using SPSS 22.0. Three datasets will be conducted: intention-to-treat; per-protocol set; and safety dataset. The intention-to-treat refers to the patients who have been randomized; an intentional analysis will be conducted for curative effect. The per-protocol set refers to all cases that do not violate the protocol and complete the trial; per-protocol set analysis will be conducted for curative effect. The safety dataset refers to the randomized cases that have taken a tested drug at least once with safety evaluation data after treatment. We use mean ± standard deviation (SD) for continuous variables and percentages for categorical variables. In measured indices, the independent t-test will be used for hypothesis testing of the normal variables, while the Wilcoxon rank sum test will be used for hypothesis testing of the skewed variables. The χ^2^ test will be used for hypothesis testing of the counted indices. The statistical analyses will use the two-sided hypothesis test. *P* ≤ 0.05 will be set as the significant level.

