**Methods/design:**

In this study, a randomized, double-blind, double-dummy, parallel control of positive drug, multicenter clinical study will be established. A total of 252 patients with acute uncomplicated lower UTI (syndrome of dampness-heat in the lower jiao) will be randomly allocated in the ratio of 1:1:1 to three groups: experimental group; control group 1; and control group 2. The experimental group receives Sanjin tablets plus levofloxacin tablets (LT) placebo; the control group 1 receives LT plus SJT placebo; and the control group 2 receives SJT plus LT on the first five days, SJT plus LT placebo on the last two days. Each group will be treated for seven days and followed-up 1–2 times. The primary outcome measures of effective rate and recurrence rate are symptoms. Secondary outcome measures of effective rate and recurrence rate are the urine leukocytes, bacteriology examination, and safety assessment. Outcomes will be assessed at baseline and after treatment.

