## Method/design

### Objective and design

This is a randomized, double-blind, double-dummy, parallel control of positive drug, multicentre clinical study. The study will be conducted at: the XiYuan Hospital, China Academy of Chinese Medical Sciences; the Longhua Hospital Shanghai University of Traditional Chinese Medicine; the Guangdong Provincial Hospital of Traditional Chinese Medicine; the Hubei Hospital of Traditional Chinese Medicine; the Affiliated hospital of Chengdu University of Traditional Chinese Medicine; and the Yunnan Provincial Hospital of Traditional Chinese Medicine. Ethical clearance for the trial was obtained from ethics committee of the six hospitals. Patients with acute uncomplicated lower UTI will undergo a standardized baseline evaluation before treatment, comprising detailed history taking, physical examination, and laboratory testing. All included patients are randomly divided into three groups: experimental group; control group 1; and control group 2. The experimental group receives SJT plus levofloxacin tablets (LT) placebo; control group 1 receives LT plus SJT placebo; and control group 2 receives SJT plus LT on the first five days, SJT plus LT placebo on the last two days. After seven days of treatment, the efficacy and safety of three groups will be evaluated. The first aim is to determine whether SJT can reduce the use of antibiotics (control group 2 versus control group 1, non-inferiority test); the second aim is to determine whether SJT can substitute the use of antibiotics (experimental group versus control group 1, non-inferiority test). The recurrence rate will be assessed at the 28-day follow-up after being cured to determine whether SJT can reduce the recurrence rate. The trial is conducted in accordance with the World Medical Association Declaration of Helsinki and Good Clinical Practice of Pharmaceutical Products [17, 18]. After a full explanation by the clinicians, written informed consent will be obtained from the participants before intervention [19, 20]. Strict data management and quality control will be conducted in this trial [21, 22]. This trial was registered in the Clinical Trials USA registry (registration No. NCT03658291) on 4 September 2018 and will be carried out from January 2019 to December 2019. The study design is shown in Fig. 1. The protocol follows the recommendations of the SPIRIT initiative (see Additional file 1) [23] and the trial results will be reported according to the latest version of the CONSORT statement [24].

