#### Primary outcome measure

The symptoms of acute uncomplicated lower UTI will be assessed. The assessment tools for symptoms of acute uncomplicated lower UTI are three participant self-rating scales (see Additional file 2): criteria sheet for evaluating the severity of urinary system infection (CSESUSI; mild: total score ≤ 8, moderate: total score 9–15, severe: total score ≥ 16), if the severity of the disease decreases from severe to moderate, or from moderate to mild, the symptoms are improved; symptoms score sheet of TCM (SSST; cure: total score = 0, effective: total score 0–6, invalid: total score ≥ 6); overactive bladder symptom score (OABSS; if the urgent urination score > 2 and total score > 3, OAB will be diagnosed; mild: total score ≤ 5, moderate: total score 6–11, severe: total score ≥ 12). The CSESUSI will use a scoring method to record the changes of symptoms and signs before and after treatment, such as shivering, fever, dysuria, urinal pain, urinary urgency, urinary frequency, lower abdomen distending pain, lumbago, and percussion tenderness over kidney region. The SSST uses a scoring method to record the changes of symptoms, tongue, and pulse in TCM before and after treatment. The OABSS has been found to be reliable and valid and highly responsive to treatment-related fluctuations in overactive bladder symptoms. Repeating the test after an acceptable treatment interval is an effective way to assess the efficacy of a particular drug regimen on OAB symptoms [33, 34]. If the symptoms disappeared after seven days of treatment, it indicates that the patient is cured. If these symptoms partially disappeared after seven days of treatment, it indicates that the treatment is effective but not cured. If there was no obvious remission and the symptoms of infection persisted after seven days of treatment, it indicates that the treatment is invalid.

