### Safety assessments

Safety measurements included laboratory indices and AEs. All patients will undergo the following laboratory examination before enrollment and at the end of the clinical trial. Changes in laboratory indices before and after the clinical trial will be compared to conducting a safety analysis. Laboratory indices are: (i) routine blood and urine testing; (ii) liver function (AST, ALT, TBIL, DBIL, γ-GT, ALP) and kidney function (Scr, BUN); and (iii) ECG. The occurrence of any AEs in trial participants, such as subjective discomfort of patients and abnormal laboratory results, will be recorded in the CRF during the whole trial process. We will withdraw patients who have severe AEs, as it will be unsafe for them to continue the trial. Meanwhile, we will give them relevant medical care and follow them up until the reaction has terminated.

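### Continuous scores, urine leukocytes and laboratory values get unadjusted t or rank sum tests although baseline values are collected: a loss of precision, not a bias

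*Protocol article*

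**What the plan says.** The Data analysis section assigns tests by type of variable. For measured variables, "the independent t-test will be used for hypothesis testing of the normal variables", and "the Wilcoxon rank sum test will be used for hypothesis testing of the skewed variables". For categorical results the χ² "test will be used for hypothesis testing of the counted indices". No baseline covariate, centre effect or regression model is named. The section does not say whether the t-test is applied to day-7 values or to changes from baseline.

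The baseline data exist. The abstract (Methods/design) says "Outcomes will be assessed at baseline and after treatment". Under Outcome measures, Primary outcome measure, the CSESUSI is used "to record the changes of symptoms and signs before and after treatment", and the SSST is described in similar terms. Under Safety assessments, "Changes in laboratory indices before and after the clinical trial will be compared". Objective and design adds that patients "will undergo a standardized baseline evaluation before treatment", and it lists six hospitals.

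The outcome that sizes the trial is of another kind. Sample size takes the effective rate as the main outcome. The Outcome measures section sorts symptoms, urine leukocytes and bacteriology into categories such as cured, effective or invalid.

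**The concern.** When a measure is recorded at baseline and again after treatment, part of the spread in the later value is usually predictable from the earlier one. A two-sample t or rank sum test on the later value leaves that spread in the error term. A t-test on the change uses the baseline, but with its slope fixed at one, which is seldom the best slope. Either way the interval is wider than the data require, and a chance imbalance in baseline severity is not handled as well as it could be.

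The article names these tests, so this is a comment on a stated choice and not on a detail left to an analysis plan. At stake is precision for the continuous summaries of CSESUSI, SSST, OABSS, urine leukocytes and laboratory indices. Validity is not at stake: under randomisation the unadjusted comparison is unbiased and its type I error is not inflated by leaving out the covariate.

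A side issue is that the choice between t and rank sum depends on whether a variable proves normal or skewed. SSST defines cure as a total of zero, so day-7 scores may cluster there, and the test would then be settled only once the data are seen.

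**Working it through.** **Plan's own figure.** The article gives no SD, correlation or target difference for any continuous measure, so there is nothing to reproduce for them. Its 76 per group (Sample size) belongs to the effective rate. That figure cannot be derived from the stated inputs, because neither a comparator rate nor a margin is given, and it does not bear on this point. It is used below only as a scale, together with 252/3 = 84 per group as planned.

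**Assumption.** ρ, the correlation between baseline and day-7 value, is not in the documents. The range shown is 0.3 to 0.6.

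**Formulas.** Take the same SD at both times and set the variance of a t-test on day-7 values to 1.
- t-test on change: 2(1 − ρ)
- ANCOVA: 1 − ρ²
- ANCOVA relative to change: (1 − ρ²) / [2(1 − ρ)] = (1 + ρ)/2

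| ρ | ANCOVA v day-7 t-test | ANCOVA v change t-test |
|---|---|---|
| 0.3 | 1 − 0.09 = 0.91 (9% less) | 1.3/2 = 0.65 (35% less) |
| 0.5 | 1 − 0.25 = 0.75 (25% less) | 1.5/2 = 0.75 (25% less) |
| 0.6 | 1 − 0.36 = 0.64 (36% less) | 1.6/2 = 0.80 (20% less) |

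The two columns move in opposite directions. At low ρ the change score is the poor choice; at high ρ the day-7 value is. ANCOVA is no worse than either. With unequal SDs σ₀ (baseline) and σ₁ (day 7), the variance of the change exceeds that of ANCOVA by (σ₀ − ρσ₁)², which is never negative, so the ordering does not depend on equal SDs, though the percentages do. At ρ = 0 ANCOVA gains nothing over the day-7 test.

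**In patients.** Against the day-7 t-test, 76 per group analysed by ANCOVA is worth 76/0.91 = 83.5 to 76/0.64 = 118.8 per group.

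**In power.** With 84 per group, two-sided α 0.05 and a true difference of 0.4326 SD (80% power for the day-7 t-test):

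| ρ | day-7 t | change t | ANCOVA |
|---|---|---|---|
| 0.3 | 0.80 | 0.66 | 0.84 |
| 0.5 | 0.80 | 0.80 | 0.90 |
| 0.6 | 0.80 | 0.88 | 0.94 |

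Simulation (3,000 trials per value) agreed: 0.79/0.65/0.82 at ρ = 0.3 and 0.80/0.79/0.89 at ρ = 0.5.

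**The effective rate, for comparison.** Two-arm trials were simulated with 76 per group and 77.14% effective (1,500 per scenario). The risk difference standardised from a logistic model with one baseline score and six centres was compared with the raw one. The strengths of the covariates are assumptions.

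| Log-odds per SD of baseline score | Centre SD (log-odds) | Variance ratio, adjusted/raw |
|---|---|---|
| 0 | 0 | 1.05 |
| 0.5 | 0.3 | 1.00 |
| 0.8 | 0.4 | 0.95 |
| 1.1 | 0.5 | 0.87 |

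So the effect runs from a 5% loss to a 13% gain, and two of the four scenarios show no gain.

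**The case against.** The strongest objection is one of relevance. The endpoints that carry the aims are categories: cured, effective or invalid; cleared or not; relapsed or not. Even the severity scales and urine leukocytes are cut into classes. These go to the χ² test, and no efficacy endpoint is defined as a mean score. A reader might infer that the t-test sentence weakens the non-inferiority comparisons, or that the 9% to 36% applies to them. The documents do not support that: the quoted test does not govern the effective rate. This part of the objection stands in full.

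Second, the wording on changes under Primary outcome measure and Safety assessments may mean that the tests are run on change scores. A reader might say that the plan throws the baseline away; the article does not establish that. This stands as a limit on wording, but the point survives, because ANCOVA beats the change-score test as well.

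Third, the size is uncertain. If most patients reach zero by day 7, ρ could be small and the gain over the day-7 test slight. This also stands. Low ρ is, however, where a change-score test does worst.

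Fourth, randomisation as described is not stratified by centre, so the design does not require a centre term. That is right, and centre is therefore optional.

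Fifth, the article is condensed, and a separate analysis plan may add adjustment. That would resolve the matter, but the article does name the unadjusted tests. For safety laboratory values, the gain in efficiency is of little practical consequence.

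**Conclusion.** The point holds as an efficiency improvement for the continuous measures. Baseline values are collected, the named tests include no covariate, and precision is lost for any non-zero ρ if day-7 values are compared. If changes are compared, it is lost unless the regression slope on baseline happens to equal one. At an assumed ρ of 0.3 to 0.6 and equal SDs, ANCOVA has 9% to 36% less variance than the day-7 t-test and 35% to 20% less than the change-score t-test. The real figure cannot be fixed from the article.

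It is not an error: no bias and no inflated type I error follow from the stated tests. Nor does it undermine the main comparisons. For the effective rate, adjustment changes the variance by a factor between 1.05 and 0.87 under assumed covariate strengths, so at most a modest gain, with a small loss if the covariates are not prognostic. Severity is minor.

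**What to change.** In the Data analysis section, state that CSESUSI, SSST and OABSS scores, urine leukocytes and laboratory values are analysed by ANCOVA of the post-treatment value on treatment and baseline value, with centre as an optional further term. Where values are skewed or pile up at zero, use a proportional-odds model with the same covariates. Assign the model to each measure before unblinding, so that the choice does not wait on the observed distribution. Keep the t and rank sum tests as sensitivity analyses.

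Adjusting the risk difference in effective rate for baseline severity is optional and should be decided in advance, given its small expected effect in either direction.

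The cost is a few lines of text and slightly more analysis work. No new data, visits or patients are needed.

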### Sample size

The effective rate will be taken as the main outcome measure of the clinical trial. According to a previous study, it showed that the effective rate of SJT was 77.14% in the treatment of simple bacterial lower urinary tract infection [25]. On the basis of a 0.9 power to detect a significant difference (α = 0.01, two-sided), 76 participants will be required for each group. 228 participants will be required for the three groups in a 1:1:1 ratio. Considering a 20% drop-out rate, we plan to include 252 patients in the whole trial.

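### Both efficacy aims are non-inferiority tests, but the sample size is justified by a difference test at two-sided α = 0.01 and the rates are analysed by a two-sided χ² test at 0.05

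*Protocol article*

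**What the plan says.** **Aims.** Objective and design sets out two efficacy comparisons, and the Discussion repeats them. The first asks whether SJT can reduce antibiotic use ("control group 2 versus control group 1, non-inferiority test"). The second asks whether SJT can replace antibiotics ("experimental group versus control group 1, non-inferiority test").

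**Sizing.** Sample size takes the effective rate as the main outcome and cites one rate, 77.14% for SJT. It then reaches 76 per group, 228 in all: "On the basis of a 0.9 power to detect a significant difference (α = 0.01, two-sided"). After an allowance for drop-out the total is 252, or 84 per group.

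**Analysis.** Data analysis assigns counted indices to the χ² "test will be used for hypothesis testing of the counted indices. The statistical analyses will use the two-sided hypothesis test". It then fixes the level: P "≤ 0.05 will be set as the significant level". The effective rate is a counted index, so this is the only test the article provides for the two aims.

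**The concern.** The three sections describe different hypotheses. The aims ask whether a test arm is not unacceptably worse than levofloxacin. The sample size and the χ² test ask whether two rates differ at all.

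A χ² test of equality contains no margin. A non-significant result does not show non-inferiority, because it may only reflect a small trial. A significant result does not rule non-inferiority out either, because a small real deficit can lie inside an acceptable margin. The conclusion at stake is whether SJT can reduce or replace an antibiotic, and the risk is that absence of a significant difference comes to be read as support for it.

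There is also a plain conflict of levels: 0.01 in Sample size against 0.05 in Data analysis. The 90% power is attached to the first level and to the difference hypothesis, so it says nothing about the chance of success on either aim.

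**Working it through.** **Inputs from the article.** SJT effective rate p = 0.7714; power 0.90; two-sided α 0.01 (Sample size) and 0.05 (Data analysis); 76 per group; 252/3 = 84 per group randomised. A comparator rate and a margin are not given, so those used below are assumptions.

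**1. Can 76 be reproduced?** Not forwards, because only one rate is stated. Solved backwards, at least two unstated settings fit.

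- *Difference test, 77.14% against 97.14% (20 points), two-sided 0.01, unpooled variance:* n = (2.576 + 1.282)² × (0.7714×0.2286 + 0.9714×0.0286)/0.20² = 14.88 × 0.2041/0.04 = 75.9, so 76. With the pooled-null formula the same rates give 80.9, so 81.
- *Non-inferiority, both arms 77.14%, 20-point margin, one-sided 0.05:* n = (1.645 + 1.282)² × 2×0.7714×0.2286/0.20² = 8.564 × 0.3527/0.04 = 75.5, so 76.

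The second setting matches neither stated alpha. With one-sided 0.005, the counterpart of two-sided 0.01, a 20-point margin needs 14.88 × 0.3527/0.04 = 131.2, so 132 per group.

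**2. Power of 76 per group for non-inferiority.** Assume both true rates are 77.14%. The standard error is √(2×0.7714×0.2286/76) = 0.0681, and power = Φ(M/0.0681 − z).

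| Assumed margin M | One-sided 0.025 (z = 1.960) | One-sided 0.005 (z = 2.576) |
|---|---|---|
| 10 points | Φ(1.468 − 1.960) = 31% | Φ(1.468 − 2.576) = 13% |
| 15 points | Φ(2.202 − 1.960) = 60% | Φ(2.202 − 2.576) = 35% |
| 20 points | Φ(2.936 − 1.960) = 84% | Φ(2.936 − 2.576) = 64% |

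Margin needed for 90% power: (1.960 + 1.282) × 0.0681 = 22.1 points, or (2.576 + 1.282) × 0.0681 = 26.3 points.

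With all 84 per group analysed, power at one-sided 0.025 is 34%, 64% and 87%. If levofloxacin is truly better, power is lower. With control assumed at 85%, SJT at 77.14% and 76 per group, it is 5%, 20% and 48%.

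**3. How often χ² would show no significant difference when SJT is truly worse.** Computed exactly from two binomials, uncorrected χ² at 0.05, 84 per group:

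- SJT 77.14% against 87.14%: non-significant about 60% of the time.
- SJT 77.14% against 92.14%: about 21%.
- If 77.14% is instead the control rate, and the test arm is 10 or 15 points lower: about 69% and 43%.

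**The case against.** The strongest defence is that this is a condensed article. The full protocol or analysis plan may hold a margin and a confidence-interval rule, and the analysis paragraph is generic: it also covers recurrence and other counts, for which a two-sided χ² test is suitable. That defence stands for the absent margin and comparator rate, which alone would not be a finding. It does not remove what the article does state: a sizing hypothesis and an alpha that disagree with its own aims and its own analysis level. Further detail elsewhere cannot make those statements agree.

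Two stronger readings are tempting and are not supported.

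- A reader might infer that 76 came from a difference calculation of 77.14% against 97.14%. The article gives neither the second rate nor the difference, the match depends on the variance formula, and a non-inferiority calculation fits equally well. The origin cannot be settled from the text.
- A reader might infer that the investigators intend to treat P > 0.05 as non-inferiority, or that this is their only route to a claim. The article nowhere says so, and it names a non-inferiority test for each comparison. The supportable statement is that the analysis section provides no test matching those aims, which leaves room for the misreading.

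It is also fair to object that the figures depend on assumed rates and margins. They are illustrations of size, not estimates of this trial's power.

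**Conclusion.** The contradiction is in the text and needs correcting. The aims are non-inferiority; the stated basis for 76 per group and 90% power is a difference at two-sided 0.01; the stated test for rates is a two-sided χ² at 0.05. That test cannot establish either aim, and the 90% figure does not apply to them.

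The size of the shortfall depends on a margin that the article does not give. Under equal true rates of 77.14% and 76 per group, 90% power is reached only at about 22 points (one-sided 0.025) or 26 points (one-sided 0.005). At 10 to 15 points it is 31% to 60%, or 13% to 35%. Correcting the alpha alone would not repair the plan, and neither would replacing the test alone. The problem concerns the two efficacy aims and does not extend to the χ² test for recurrence.

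**What to change.** **Data analysis.** For the two efficacy aims, replace the χ² test with the two-sided confidence interval for the risk difference in effective rate (test arm minus control group 1), at a level that matches the single chosen alpha. Claim non-inferiority only if the lower limit lies above −M, where M is stated and clinically justified in advance. Report this in the intention-to-treat and per-protocol sets already planned. Add a sentence that a non-significant χ² result supports no non-inferiority claim. Keep the two-sided χ² test for recurrence and other counted indices.

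**Sample size.** Replace the wording on detecting a difference with the non-inferiority hypothesis, its assumed control rate and M. Use the same alpha in both sections. Restate the power that 252 patients give for that M.

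**Cost.** The correction itself is a change of wording, to be made before unblinding. The power quoted is likely to fall. If the justified margin is 10 to 15 points, the trial may be unable to conclude non-inferiority at this size, and the protocol should say so.
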